### Study interventions

The specific details of the interventions received by study arms: 1) Loozit^® ^group program 'G' only; and, 2) Loozit^® ^group program 'G' plus additional therapeutic contact 'ATC' i.e. 'G+ATC', are as follows:

#### 1) Loozit^® ^group program (G)

##### i) Background

The key aspects covered in the Loozit^® ^group program are in keeping with Australian clinical guidelines for the management of overweight and obesity [32] and include healthy food choices and eating patterns, increasing physical activity and reducing sedentary behaviour, strategies for managing behaviour change with a focus on goal setting, dealing with stress and building self-esteem. The program is based upon a cognitive behavioural approach using behavioural principles to change dietary intake and activity levels, and social cognitive approaches to modify self-efficacy, motivation, perseverance and self-regulation [37].

Participants in both arms of this study receive the Loozit^® ^group program (G) which is provided separately to adolescents and their parents/carers. Separate skills training sessions for parents have been shown to help weight loss in adolescents [38], and this approach was requested by both parents and adolescents in focus groups held as part of the pilot study that preceded the current study [31]. The Loozit^® ^group program is run over a 24 month period and is divided into two distinct phases. Phase 1 consists of seven group sessions for adolescents and their parents/carers that take place weekly for seven consecutive weeks during a school term. This is followed by phase 2 which involves a further seven group sessions for adolescents, called 'booster' group sessions, held once every school term (approximately once every three months to 24 months post-baseline).

##### ii) Phase 1 – Adolescent and parent weekly group sessions

###### a) Format

Separate but simultaneous group sessions are held for adolescents and their parents/carers in the evening. Group sessions are facilitated by dietitians (but could be run by nurses or other health professionals) and each group typically has between five and nine members. Usually one parent/carer from each family attends but there are no restrictions on parent/carer numbers. Parents/carers are not permitted to bring younger children to the group sessions in order to minimise disruption. Due to budgetary constraints we are unable to provide child minding facilities for adolescent's siblings. The general structure of an adolescent and parent group session is outlined in Table 2.

**Table 2 T2:** Structure of weekly group sessions in phase 1 of the Loozit^® ^group program

**Adolescent session**	**Time** **(mins)**	**Parent session**	**Time** **(mins)**
i) Reconnect with group (includes an icebreaker) and review progress with goals	15	i) Reconnect with group and review progress with family goals	15
ii) Resistance activities	10	ii) Facilitator-led discussion on set topic^a^	50
iii) Facilitator-led discussion on set topic^a^	30	iii) Recap important points and record family goals for the week ahead	10
iv) Recap important points and record individual goals for the week ahead	10		
v) Fun active game and light refreshments	10		
Total	75	Total	75

^a ^See additional file 1: Phase 1 of the Loozit^® ^group program – weekly topics and key content

###### b) Content

For a summary of the topics and key content of the facilitator-led discussion in each weekly session (see additional file 1: *Phase 1 of the Loozit^® ^group program – weekly topics and key content*). The group sessions are designed to provide education, to promote adolescent skill development, to encourage group interaction, and to foster peer bonding. The main difference between the structure and content of the adolescent and parent group sessions is that those for adolescents promote physical activity skills development through approximately 20 minutes/session of indoor resistance activities and fun active indoor games. Adolescents also spend more time discussing self-esteem and stress management and have a practical session involving the preparation and tasting of healthy foods. The parent sessions focus on practical support of behavioural change in adolescents and parental role modeling of healthy lifestyle changes for the family unit. By the end of phase 1 adolescents and parents/carers have largely covered the same material.

###### c) Goal setting

In the initial session, adolescents and parents/carers are taught how to set "SMART" goals that are ***s***pecific, ***m***easurable, ***a***chievable, ***r***ealistic, and can be attained in a fixed ***t***ime frame. Towards the end of each group session, adolescents are given time to set an individual SMART goal for the week ahead that relates to the current or previous session. Adolescents record their goal on a brightly coloured, take home, 'UZIT' worksheet. Similarly, at the end of each group session parents are given time to set 'family goals' that are recorded in the parent booklet; an example of such a goal would be to have three family meals at the table with the television turned off that week. At the beginning of the adolescent and parent group sessions, facilitators encourage group members to report to the group on their progress with their goals and individual strategies in order to support and educate each other. Success and effort is praised, and facilitators encourage group discussion on solutions to overcoming the barriers to goal achievement.

###### d) Resources

The Loozit^® ^group program is delivered using a limited array of inexpensive resources in line with the concept of sustainability. Separate, specially developed booklets for adolescents and parents/carers are used during the sessions to support learning and include a summary of the key information discussed, along with space for occasional written activities and recording goals. Parents/carers are given their booklets to take home each week, whereas the adolescents' booklets are collected at the end of each session by the group facilitator to ensure they will be available at each session. At the end of phase 1, adolescents are given their booklets to keep at home. The resistance-based physical activities do not require equipment other than tinned food cans which are used as inexpensive hand weights. Basic equipment is used for a variety of fun active games including skipping ropes, rubber balls, and balloons. Adolescents are also encouraged to introduce their own fun games and bring along their favourite music to play during the game time. The resources used for the adolescent cooking activity include common kitchen utensils, serving plates, and the venue's microwave. Selected food models and food packages are used for educational demonstrations. Light refreshments are provided at each group session.

##### iii) Phase 2 – Extended therapeutic contact (adolescents only)

###### a) Format and content

At the completion of phase 1, adolescents in both study arms enter phase 2 which involves extended therapeutic contact and forms the maintenance component of the Loozit^® ^group program 'G'. Phase 2 involves seven group sessions, held approximately once every three months in the middle of the school term (four terms per year), comprising five × 60 minute 'booster' group sessions and an outcome assessment session at 12 and 24 months post-baseline (see additional file 2: *Phase 2 of the Loozit^® ^group program – 'booster' session topics and key content*). The main educational content of the booster group sessions is generally new, although the key messages from phase 1 are reinforced (see additional file 1: *Phase 1 of the Loozit^® ^group program – weekly topics and key content*). Booster group sessions have a structure similar to the group sessions held in phase 1 (Table 2); however the amount of time spent on various components is less. For example, more time is spent on the fun group building activity and less time is spent on the facilitator-led discussion. No extended therapeutic contact is offered to parents/carers.

###### b) Practical considerations

In order to preserve 'booster' group numbers when attrition occurrs, it was decided that groups allocated to the same study arm, from various cohorts that attended the same venue, should be combined. In order to prevent contamination between the two study arms, participants in the 'G' and 'G+ATC' interventions are never put together in the same group. This combining of groups in the maintenance phase also permits an informal peer support system where participants in the latter stages of the program provide an example and encouragement for participants in the early stages of phase 2.

#### 2) Additional therapeutic contact for adolescents (ATC)

##### i) Background

In addition to the Loozit^® ^group program 'G', participants in the 'G+ATC' study arm also receive a modest level of additional therapeutic contact (ATC) in phase 2 only. ATC is planned communication from the group facilitator to the adolescent via telephone coaching plus a mode of electronic communication i.e. mobile phone SMS or e-mail messages, or both, according to adolescent preference. The aim of ATC is to enhance adolescents' knowledge, skills and confidence to initiate and maintain required changes in dietary and activity behaviours. Because mobile phone SMS and e-mail interventions are relatively new technologies, there is little evidence in the child and adolescent weight management literature on the optimum frequency of contact and level of interaction in using these technologies, especially in the context of a program that already offers extended therapeutic contact in the form of group sessions and telephone coaching. A primary consideration in the design of the ATC schedule was that it was in keeping with the sustainability aspects of the Loozit^® ^group program. Parents/carers of adolescents in the 'G+ATC' study arm do not receive any form of ATC.

##### ii) Format

The schedule for ATC covers a 10 week school term period and the following holiday period (Table 3). Throughout the study the schedule is repeated seven times, totaling 32 electronic communication messages and potentially 14 telephone coaching calls over approximately 21 months.

**Table 3 T3:** Quarterly schedule for additional therapeutic contact (ATC) in the 'G+ATC' intervention group^a^

**Quarterly schedule**	**Mode of ATC**
***School term week***	
1, 4, 6, 9	No contact
2 & 7	10 minute telephone coaching call with adolescent
3, 8,10	Group facilitator sends adolescent an email message and/or mobile phone SMS according to preference
5	Booster group session

***End of term school holiday week*^b^**	
1	No contact
2	Group facilitator sends adolescent an email message and/or mobile phone SMS according to preference

^a ^This schedule is repeated seven times during phase 2 of the study

^b ^Once a year students have a six week summer holiday. During this period they receive ATC once a fortnight via mobile phone SMS and/or e-mail, totaling 3 contact occasions.

##### iii) Telephone coaching

Telephone coaching is formalised communication between the adolescent and the group facilitator and is adapted from that used in a study involving adolescents with type 1 diabetes [39]. Semi-structured telephone coaching calls are designed to be approximately 10 minutes in duration with elements to: a) establish rapport; b) collaborate to identify behavioural goals related to topics covered in the group program (or previously identified by the adolescent); c) identify barriers to achieving goals; d) assist in problem solving; and e) provide positive encouragement for further change [39]. If the adolescent is not contactable, facilitators continue to attempt to contact the adolescent in line with the developed protocol.

##### iv) Mobile phone SMS and e-mail messages

Mobile phone SMS and e-mail communications are researcher-initiated short messages (less than 160 characters) that cover the important points raised during phase 1. The messages follow a set schedule so that all participants receive the same messages. To encourage interactivity approximately two-thirds of the messages end with 'please reply' for example, *"Everywhere is within walking distance if you have the time" How could you be more active this week? Please reply"*. If a response is received from an adolescent, the facilitator is permitted one reply message that is individually tailored with the purpose of providing positive reinforcement, education and encouragement.

##### v) Protocols

Detailed written protocols are followed for the semi-structured telephone coaching and the pre-determined content of the mobile phone SMS and e-mail messages. These were developed based upon those used in studies with adults and adolescents with type 1 diabetes [39,40]. Facilitators keep a detailed record of ATC implementation including delivery medium, time/duration, and content of every contact initiated with adolescents. The same details are recorded for all responses from adolescents. Strict protocols have been developed to guide facilitators in the event of a child protection, mental health or other major issue being raised during ATC.

##### vi) Adolescent ATC preferences

Adolescents' ATC preferences regarding the day/s and time/s that they wish to receive telephone coaching calls, as well as their preference to receive mobile phone SMS and/or e-mail messages is determined at the two month outcome assessment session at the end of phase 1. ATC preferences are reassessed at the 12 month outcome assessment session. Adolescent contact details relevant to ATC are collected at the end of phase 1 and these are checked on a regular basis i.e. during the telephone coaching sessions and at the 12 month outcome assessment session.

### Intervention sites

Community Health Centres or local government community centres at a range of sites in Sydney, Australia, have been approached with regards to the potential of using group rooms for phase 1 and 2 of the Loozit^® ^group program over two years. Each venue requires a room large enough to use for indoor active games and resistance exercise activities, adequate parking, and access to a microwave and sink for the adolescent cooking session. Although proximity to public transport is a consideration, the vast majority of families travel to the groups by private vehicle. Many of the venues have free parking. When there is a parking charge participants are given a voucher to cover expenses.

### Quality control

#### Staff training

Group facilitators (and outcome assessors) receive standardised training. A facilitators' manual contains detailed information specific to each group session including a script for the educational material, timing of each component, the type of resistance activities to be performed, suggestions for various fun active games, and a list of the resources required. Group facilitators attend a weekly meeting with the project manager to ensure protocol adherence.

#### Evaluation of group sessions

Facilitators complete a standardised evaluation form after each group session to record parent/carer and adolescent attendance at group sessions and the degree of compliance with the facilitator's manual during the group session.

### Measures

#### Schedule

The primary outcomes are adolescent BMI z-score and waist circumference z-score. The secondary outcomes are metabolic profile indicators, physical activity, sedentary behaviour, food intake, eating patterns, and various aspects of adolescent psychosocial wellbeing. All these outcomes are measured at baseline, 2 months post-baseline (end of phase 1), 12 months post-baseline (almost half-way through phase 2), and 24 months post-baseline (at the end of phase 2). In addition, at 2, 12 and 24 months post-baseline, adolescent and parent/carer satisfaction with the program is measured by questionnaire.

#### Measurement tools and procedures

##### i) Anthropometry and blood pressure

Trained staff members, who are blinded to treatment allocation, measure adolescents' anthropometry and blood pressure (BP) using standard procedures and calibrated instruments. Weight is measured with portable scales (Tanita HD-316, Tanita Corp.;Tokyo, Japan) to the nearest 0.1 kg, with shoes and heavy clothing removed. Height is measured to the nearest 0.1 cm using a fixed stadiometer at The Children's Hospital at Westmead (Holtain Limited; Crymych, Dyfed, Britain) or a portable stadiometer (Seca, Model 220; Germany) when measurements are conducted at Community Health Centres. Waist circumference is measured at the narrowest point between the lower costal (rib) border and the iliac crest using a nonextensible steel tape. BMI and waist circumference z-scores will be calculated based upon age- and sex-specific reference values [41,42]. Systolic and diastolic BP are measured using an automated BP monitor (Dinamap model 8101, Critikon Inc.; Florida, USA) under standard conditions [43]. All of these measurements take place in a private room.

##### ii) Metabolic bio-markers

A 20 ml fasting blood sample is collected by a nationally accredited external pathology laboratory (also blinded to the adolescent's treatment allocation) which has many collection sites in the study region. The blood sample is analysed for cholesterol (total, HDL & LDL), triglycerides, insulin, glucose and liver function indicators using standard automated techniques in that laboratory.

##### iii) Adolescent self completed questionnaires

The following questionnaires are completed by adolescent participants, in a room with other members of their group, supervised by a group facilitator. Together these questionnaires take between 30–45 minutes to complete.

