#### Eligibility criteria

The inclusion and exclusion criteria for assessing adolescent eligibility to participate in the study (Table 1) are used during a telephone screen that is conducted with whoever enquires about the study (e.g. parents/carers, adolescents, health professionals or school counselors). Each enquiry about study participation is issued with a unique identification number that is used to distinguish individuals throughout the study. Adolescents who meet the study criteria are invited to an appointment with a research assistant, along with their parents/carers, in order to confirm eligibility based on objectively measured weight status. Informed consent or assent, depending on age, is obtained from adolescents who meet the study eligibility criteria and wish to participate. Consent is also obtained from one of the adolescent's parents/guardians. Although many adolescents are found to be ineligible during the telephone screen, it is uncommon for adolescents to be found ineligible at the appointment. Adolescents who are ineligible to participate, and their parents/carers, are encouraged to follow up with their general practitioner.

**Table 1 T1:** Inclusion and exclusion criteria for adolescent participation in the Loozit^® ^study

**Inclusion criteria**	**Exclusion criteria**
▪ Age 13.0–16.9 years	▪ Severely obese (i.e. BMI z-score^a ^>2.5) or if there is a secondary cause for overweight/obesity
▪ Overweight to moderately obese (i.e. BMI z-score^a ^range 1.0–2.5)	▪ Intellectual disability, significant medical illness, psychiatric disturbance
▪ Home access to a landline telephone	▪ Taking medications that affect weight status
▪ Home access to the internet to receive e-mails or access to a mobile phone to receive SMS messages	▪ Inability to take part in physical activity sessions
▪ Ability to attend the group program for 7 weeks in the first instance on the specified days^b^	▪ Poor level of spoken English (adolescent or parent/carer)
▪ At least one of the adolescent's parents/carers must be willing to also participate in the initial 7 parent group sessions	

^a ^calculated using Centers for Disease Control growth reference [41]

^b ^The 'G' and 'G +ATC' group programs are run on separate weeknights and therefore potential participants need to be available to attend on either evening, pending randomisation, even though they would only attend once per week

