#### Randomisation

A computer generated randomisation sequence, stratified for sex, age group (13–14 years; 15–16 years), and intervention site was provided by staff in the Clinical Epidemiology Unit, The Children's Hospital at Westmead. The trial manager is responsible for concealed allocation which involves preparing, for each intervention site, sex and age group, a set of consecutively numbered opaque envelopes containing the group allocation 'G' or 'G+ATC'. After participant consent is obtained the next numbered envelope is opened by a research assistant (at the abovementioned appointment to confirm eligibility), revealing the group allocation and this is recorded along with the individuals pre-assigned identification number. Outcome assessors are the only persons blinded to group assignment.

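### As written, the baseline self-report questionnaires appear to follow the opening of the allocation envelope, so knowledge of the arm can shift them

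*Protocol article*

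**What the plan says.** All references are to the Protocol article.

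- **Eligibility criteria:** the family attends an appointment with a research assistant "in order to confirm eligibility based on objectively measured weight status". No other measurement is named for that appointment.
- **Randomisation:** "After participant consent is obtained the next numbered envelope is opened by a research assistant (at the abovementioned appointment to confirm eligibility), revealing the group". The same section adds: "Outcome assessors are the only persons blinded to group assignment".
- **Measures, Schedule**, on the primary and secondary outcomes together: "All these outcomes are measured at baseline, 2 months post-baseline (end of phase 1"), and again at 12 and 24 months.
- **Adolescent self completed questionnaires:** these are filled in "in a room with other members of their group, supervised by a group facilitator" and take 30 to 45 minutes. Baseline is not treated separately.
- **Table 1, footnote b:** "The 'G' and 'G +ATC' group programs are run on separate weeknights", and which evening applies depends on randomisation. Under Phase 2, Practical considerations, the article adds that the two arms are never mixed in one group; this is said of the combined booster groups.
- **Additional therapeutic contact, Background:** the extra contact comes from the group facilitator and is given only in phase 2.
- **Planned data analysis:** a mixed model that accounts for baseline covariates, with further adjustment for baseline differences between arms where needed.

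**The concern.** A baseline is useful in a randomised comparison because allocation cannot have influenced it. If a self-report questionnaire is answered after the family has learned its arm, that guarantee is lost. An adolescent who expects two years of coaching, or who is disappointed not to get it, may describe activity, diet or self-worth differently. The facilitator in the room also knows the arm and, in G+ATC, will deliver the extra contact. The direction of such a shift is not known.

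The stake is the self-reported secondary outcomes. Hypothesis 1b rests on their change from baseline within each arm, hypothesis 2 claims a between-arm difference on them, and the Harter global self-worth score is named in the Sample size section. A between-arm baseline difference found by the planned test could then be a consequence of allocation rather than chance, and adjusting for it would not fully restore comparability.

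There is a second consequence. An adolescent who leaves between the envelope and the first group meeting would have no questionnaire baseline, although already randomised. Blinded assessors at later visits can repair neither problem.

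**Working it through.** **1. The order of events.** No arithmetic decides this; the sections have to be set side by side.

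1. Consent and the opening of the envelope take place at the same eligibility appointment (Eligibility criteria; Randomisation).
2. The only measurement named for that appointment is weight status, which confirms eligibility and so comes before the envelope.
3. The questionnaires have a baseline administration (Schedule).
4. They are completed with the adolescent's group under a group facilitator, with no exception for baseline (Adolescent self completed questionnaires).
5. The group is defined by arm (Table 1, footnote b; Practical considerations), so it does not exist for an adolescent until the envelope is opened.

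Steps 1, 4 and 5 together put the baseline questionnaires after disclosure. Nothing in the article gives the opposite order.

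**2. The plan's own figure.** The sample size is needed only as the n for the illustration below. Inputs from Sample size: difference 0.4, SD 0.8, two-sided 0.05, power 80%.

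n per arm = 2 × (1.960 + 0.842)² × 0.8² / 0.4² = 62.8, so 63 by the normal approximation. The t-test gives 63.8, so 64, with 80.1% power. The stated 64 reproduces, and the order of procedures does not alter it.

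**3. Does baseline adjustment remove a post-allocation shift?** Assumptions, none from the documents: 64 per arm, equal SDs at baseline and follow-up, no true effect, a shift of s SD in one arm at baseline that does not carry to follow-up, and baseline-to-follow-up correlation r.

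- Change score: absolute bias = s; SE = √(2(1 − r)) × √(2/64).
- Baseline-adjusted: absolute bias = r × s; SE = √(1 − r²) × √(2/64).
- Type I error = Φ(bias/SE − 1.96) + Φ(−bias/SE − 1.96).

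Example, s = 0.2 and r = 0.5, with √(2/64) = 0.177:

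- Change score: SE = 1 × 0.177 = 0.177; 0.2/0.177 = 1.13; type I error 20.5%.
- Adjusted: bias = 0.5 × 0.2 = 0.10; SE = √0.75 × 0.177 = 0.153; 0.10/0.153 = 0.65; type I error 10.0%.

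| s (SD) | r | Change-score bias | Type I error | Adjusted bias | Type I error |
|---|---|---|---|---|---|
| 0.1 | 0.3 | 0.10 | 7.7% | 0.03 | 5.4% |
| 0.1 | 0.5 | 0.10 | 8.7% | 0.05 | 6.2% |
| 0.1 | 0.7 | 0.10 | 11.3% | 0.07 | 8.6% |
| 0.2 | 0.3 | 0.20 | 16.0% | 0.06 | 6.5% |
| 0.2 | 0.5 | 0.20 | 20.5% | 0.10 | 10.0% |
| 0.2 | 0.7 | 0.20 | 30.9% | 0.14 | 19.8% |
| 0.3 | 0.3 | 0.30 | 30.0% | 0.09 | 8.3% |
| 0.3 | 0.5 | 0.30 | 39.6% | 0.15 | 16.5% |
| 0.3 | 0.7 | 0.30 | 59.1% | 0.21 | 38.4% |

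Adjustment shrinks the bias by the factor r and leaves the rest. A shift that partly persisted to follow-up would give other figures, so the table shows the mechanism and does not estimate this trial's bias.

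**The case against.** The strongest reply is that the order is inferred. The sentence on the group setting introduces the questionnaires for all visits, and it cannot hold literally at each one: the satisfaction forms start at 2 months and pubertal staging is not done at 2 months. Figure 1, which summarises the design, is not available here and may show the order. A condensed article may also leave visit procedures to the full protocol. All of this stands as a limit on certainty. It does not supply a different order, and the sections that are available agree with one another.

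A second reply is that both arms receive the same phase 1 and the extra contact starts only in phase 2. That is right, and it confines the mechanism to expectation and reporting; no treatment effect can be present at baseline. A third is that families must already be free on either evening before randomisation, which weakens the idea that they leave because of the night. Early departure for other reasons remains possible, but that it would differ by arm is conjecture.

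A reader might go further and infer that the baseline blood sample also follows the envelope, because it is fasting, taken off site and needs consent. The article says "A 20 ml fasting blood sample is collected by a nationally accredited external pathology laboratory" and that the laboratory is blinded, but gives no timing, so this is not established. Nor can the point be extended to all secondary outcomes: blood pressure is taken by blinded staff on an automated monitor. Weight status, on which BMI z-score depends, is checked before the envelope is opened.

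**Conclusion.** The point holds for the self-completed questionnaires: activity, sedentary behaviour, food intake and eating patterns, the Harter profile, body image, social status and MHI-5. As the article reads, their baseline is taken after allocation is known, by adolescents and under a facilitator who are not blinded. This rests on reading several sections together and on the group setting applying at baseline as it does later.

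The size of any bias cannot be derived from the documents. It is tempting to divide an assumed shift of 0.1 to 0.2 SD by the design effect of 0.4/0.8 = 0.5 SD and report a bias of 20% to 40% of that effect. The documents do not support this. The shift is assumed, the 0.5 SD belongs to change in BMI z-score and not to these questionnaires, and the calculation ignores the planned baseline adjustment. What can be said is that adjustment reduces such a bias without removing it.

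The primary outcome BMI z-score and blood pressure are not shown to be affected. The timing of the baseline blood sample is a matter for clarification only. The change is worth making because it removes an avoidable source of bias in secondary outcomes at little cost.

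**What to change.** In Randomisation and in Adolescent self completed questionnaires, state that the baseline questionnaires are completed at the eligibility appointment, supervised by the research assistant, after consent and before the envelope is opened. This also gives every randomised adolescent a questionnaire baseline, including any who leave before the first group meeting.

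Apply this to cohorts still to be enrolled. How many remain is not stated: recruitment is described as ongoing, but completing all 24-month assessments by July 2011 implies that enrolment ends about July 2009. For earlier cohorts, report which baseline values were taken after allocation and treat this as a limitation of the self-report results.

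Separately, state when the baseline blood sample is drawn relative to the envelope. Requiring the off-site fasting draw first is not proposed, since it would delay randomisation and is not clearly cheap.

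Cost: an appointment 30 to 45 minutes longer, with no new instruments.

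### Self-reported outcomes at 12 and 24 months are completed under the unblinded role that delivers the ATC coaching, so reporting bias could differ by arm

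*Protocol article*

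**What the plan says.** Under Adolescent self completed questionnaires, the Protocol article has the instruments filled in "in a room with other members of their group, supervised by a group facilitator". They cover physical activity and sedentary behaviour, food intake and eating patterns, psychosocial wellbeing, pubertal stage and satisfaction with the program. Practical considerations adds that the two arms are never mixed, so each such group belongs to one arm.

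The Background to the ATC section states that "ATC is planned communication from the group facilitator to the adolescent via telephone coaching plus a mode of electronic communication", and that it is given in phase 2 only. Telephone coaching describes calls that build rapport, agree behavioural goals on program topics, work through barriers and encourage further change. The Format section allows up to 14 calls over about 21 months.

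On blinding, the Randomisation section says "Outcome assessors are the only persons blinded to group assignment". For the physical measures, Anthropometry and blood pressure says "Trained staff members, who are blinded to treatment allocation, measure adolescents' anthropometry and blood pressure (BP) using standard procedures and calibrated instruments", and adds "All of these measurements take place in a private room".

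Under Aims and hypotheses, hypothesis 2 claims an advantage for G+ATC on primary and secondary outcomes at 12 and 24 months.

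**The concern.** Participants cannot be blinded to coaching calls, so their own reports are always open to some bias. The plan adds an avoidable layer. The person overseeing the questionnaires holds the role that, in one arm only, has been phoning adolescents to set and review goals on the behaviours now being reported. An adolescent who knows and likes the coach may report more activity, better eating or higher self-worth than one who has met a facilitator only in group sessions.

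Most secondary outcomes outside the blood tests and blood pressure come from these questionnaires. If part of an apparent ATC benefit on them reflected whom the adolescent was trying to please, the trial could not separate it from real behaviour change. Program satisfaction is exposed in the same way, although the Schedule section lists it apart from the secondary outcomes.

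**Working it through.** The document gives no bias size, so the main check is to set the statements side by side.

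**1. Who supervises, who coaches, who is blinded**

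| Question | Answer | Section |
|---|---|---|
| Who supervises the questionnaires? | A group facilitator | Adolescent self completed questionnaires |
| Who delivers ATC? | The group facilitator | ATC, Background |
| Is that role blinded? | No; only outcome assessors are | Randomisation |
| Who else is in the room? | Members of the same, single-arm group | Adolescent self completed questionnaires; Practical considerations |

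The supervisor is therefore unblinded in both arms. In G+ATC the supervisor also belongs to the coaching role.

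**2. Which visits are exposed**

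- Baseline and 2 months: ATC has not begun, so ATC rapport cannot affect the answers.
- 12 months: about 10 of the roughly 21 months of ATC have passed. Up to about 14 × 10/21 = 6.7 calls, say 6 or 7, could have taken place. The Schedule section likewise calls this visit almost half-way through phase 2.
- 24 months: up to all 14 calls.

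**3. Whether the analysis deals with it**

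Planned data analysis specifies a mixed model with baseline covariates and between-group contrasts at each visit. A bias that arises after baseline, and in one arm more than the other, is part of the estimated group difference at 12 and 24 months. Baseline adjustment does not touch it.

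**4. Illustration of scale (bias sizes assumed)**

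First, the plan's own figure. With a difference of 0.4, SD 0.8, two-sided 0.05 and n = 64 per arm, the noncentrality is (0.4/0.8) × √(64/2) = 0.5 × 5.657 = 2.83 on 2 × 64 − 2 = 126 degrees of freedom. Power is 80.1%, so the stated 64 reproduces.

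Next, suppose the true effect on a self-reported outcome is zero and reporting adds b SD to the G+ATC mean. The noncentrality is b × √(n/2), and the two-sided rejection rate is:

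| Assumed b (SD) | n = 58 | n = 64 | n = 84 |
|---|---|---|---|
| 0 | 5.0% | 5.0% | 5.0% |
| 0.1 | 8.3% | 8.7% | 9.9% |
| 0.2 | 18.7% | 20.2% | 25.2% |
| 0.3 | 36.0% | 39.1% | 48.9% |

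Here 64 is the planned analysable number, 84 the enrolment target, and 58 is 84 less 30% (84 × 0.70 = 58.8, rounded down). The values of b are not estimates. The test is a plain t-test, not the planned mixed model. The table shows only that a modest arm-specific shift would matter at this sample size.

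**The case against.** Several points on the other side are fair.

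- **The supervisor need not be the adolescent's own coach.** The text says a group facilitator. That this is the same individual is the likely reading but is not stated. The concern rests on the role.
- **Only the increment differs.** Both arms answer under a facilitator after the same group program. Only the extra rapport from ATC can differ, and the direction assumed here, more contact leading to more favourable answers, is plausible but not shown.
- **A new supervisor does not blind the adolescent.** This is correct; the change reduces one source of bias and leaves the other. Research assistants open the allocation envelopes, so they are not blind either. What matters is that the supervisor has no coaching relationship with the group.

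A reader might go further and infer that the assessors' blinding fails. Table 1, footnote b, says the "group programs are run on separate weeknights"; the 12- and 24-month assessments are counted among the phase 2 group sessions; "ATC preferences are reassessed at the 12 month outcome assessment session"; and G+ATC alone completes an extra questionnaire at 24 months. The document does not support that conclusion. It states that assessors are blinded and that they measure in a private room. Nowhere does it say that they take ATC preferences, see the extra questionnaire, or know which night belongs to which arm. The weeknight footnote is attached to attendance at the initial seven-week program, not to the later assessments. Detailed masking procedures are also something an article commonly leaves to the full protocol. At most, these arrangements could allow unblinding.

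**Conclusion.** The point holds for the self-reported outcomes at 12 and 24 months, and for program satisfaction. The plan places an unblinded role that delivers the intervention in one arm over the completion of those questionnaires, and baseline adjustment cannot correct a bias that arises later. The 2-month visit is not affected by ATC rapport.

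The size of any bias cannot be computed from the document. The conclusion assumes that supervision by the coaching role influences answers, and more so where there has been one-to-one contact.

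It does not extend to a finding against the primary outcomes. BMI and waist z-scores are measured by staff stated to be blinded, using calibrated instruments. Blood pressure is automated, and bloods go to an external blinded laboratory. The precautions for anthropometry below guard against a possibility and do not imply that blinding has failed.

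**What to change.** Recruitment was still being described as under way, and 24-month assessments were expected to run to July 2011, so later visits could still be changed.

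1. At the remaining 12- and 24-month assessments, in both arms alike, have the questionnaires supervised by an existing research assistant or other staff member who does not coach that group.
2. Have adolescents seal completed questionnaires so that the facilitator does not see the answers, and tell them so beforehand.
3. As a precaution for waist and BMI, do anthropometry before ATC preferences or the 24-month ATC questionnaire are taken, and keep those tasks away from the assessor.
4. Have assessors record their guess of the arm at 12 and 24 months, so that the blinding claim can be examined.

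The cost is minor rostering effort, with no new staff or visits. Adolescents already enrolled would have different supervision at earlier and later visits. That affects their within-arm change from baseline, but it is the same in both arms, so the between-arm comparison is preserved. Adolescents' knowledge of their own arm remains and should be acknowledged when the self-reported results are interpreted.
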